## Abstract

**Background:**

Chronic fatigue syndrome (CFS), also known as myalgic encephalomyelitis (ME), is a debilitating condition characterized by persistent fatigue and a range of complex accompanying symptoms. While curative treatments remain limited, Tuina (a traditional manual therapy in Chinese medicine) has shown potential in alleviating fatigue in pilot studies. However, high-quality evidence from large-scale, multicenter trials regarding its efficacy and long-term sustainability is lacking.

**Objective:**

This trial aims to evaluate the efficacy and safety of Tuina combined with usual care (UC) for CFS compared with UC alone.

**Methods:**

This prospective, multicenter, randomized, open-label, assessor-blinded, parallel-group clinical trial will be conducted at 6 hospitals in China. The study consists of 3 phases: a 1-week run-in period, an 8-week treatment period, and a 24-week follow-up period. A total of 230 eligible participants diagnosed with CFS (Centers for Disease Control and Prevention 1994 criteria) will be recruited and randomly allocated (1:1) to receive either Tuina therapy plus UC (intervention group) or UC alone (control group). The intervention group will undergo 24 sessions of a standardized Tuina protocol over 8 weeks (3 sessions/week). Follow-up assessments will be conducted at weeks 4, 8, 20, and 32. The primary outcome is the change in fatigue severity measured by the 11-item Chalder Fatigue Questionnaire from baseline to week 8. Secondary outcomes include clinical response rate, sleep quality, anxiety, depression, quality of life, adverse events, and clinical global impression. Efficacy analysis will be performed using a mixed-effects model for repeated measures in the modified intention-to-treat population. Secondary outcomes will be analyzed as exploratory supportive end points using appropriate parametric or nonparametric tests based on data distribution, with week 8 defined as the main secondary time point and later follow-up visits interpreted as durability contrasts. Missing outcome data will be handled primarily through likelihood-based mixed-model estimation under a missing-at-random assumption, with multiple imputation and per-protocol analyses used as sensitivity analyses.

**Results:**

Recruitment for this trial will start in March 2026 and is expected to be completed by March 2027. The results of this study are expected to provide reliable evidence regarding the role of Tuina in the management of CFS.

**Conclusions:**

This multicenter randomized controlled trial will evaluate the effectiveness, long-term sustainability, and safety of Tuina therapy plus UC for improving fatigue, sleep, mood, and quality of life in CFS or ME. If proven beneficial, Tuina may serve as a scalable nonpharmacological option to support clinical decision-making and standardized implementation.

## Introduction

Chronic fatigue syndrome (CFS), also known as myalgic encephalomyelitis (ME), represents a significant global health challenge, characterized by persistent or relapsing fatigue and a range of complex, medically unexplained accompanying symptoms [1,2]. The global prevalence of CFS is estimated to be between 0.4% and 2.6%, and incidence rates may be rising due to modern lifestyle stressors and postviral sequelae (eg, long COVID) [2,3]. Individuals with CFS or ME may experience difficulties in working, education, and mobility. In severe cases, their condition may confine them to bed and render them dependent on care [4]. Given its unclear etiology, curative treatments remain elusive [1,5-7].

The management of CFS has traditionally emphasized graded exercise therapy (GET) and cognitive behavioral therapy (CBT) [5-7]. However, the safety of these interventions has been questioned, leading the 2021 National Institute for Health and Care Excellence (NICE) guidelines to withdraw GET due to concerns over symptom exacerbation, and downgrade CBT to a supportive role [8,9]. These limitations highlight a critical unmet need for nonpharmacological interventions that are both effective and well tolerated.

Tuina is a traditional Chinese medicine external therapy based on the fundamental theories of traditional Chinese medicine. Through specific manipulations such as pressing, kneading, and pushing on the meridians and acupoints, Tuina aims to promote the flow of Qi and blood, thereby restoring physiological balance [10]. Emerging evidence suggests that Tuina is a promising approach for alleviating CFS or ME symptoms, showing potential benefits in reducing fatigue, improving sleep quality, and alleviating anxiety and depression [11-13]. In addition, a recent systematic review and meta-analysis of massage therapy for CFS reported improvements in fatigue symptoms and few adverse reactions, although the included studies were heterogeneous and generally limited in methodological rigor [14].

However, despite these promising findings, the current evidence base remains limited. Most existing studies are characterized by small sample sizes, single-center designs, and short-term follow-ups, which may restrict the generalizability of the results [15,16]. Furthermore, the lack of standardized intervention protocols across different clinical settings poses a challenge to evaluating the consistency of Tuina’s therapeutic effects. Consequently, high-quality evidence from large-scale, multicenter trials with rigorous methodology is urgently needed to substantiate the efficacy of Tuina in clinical management for CFS or ME.

## Methods

### Objective

The primary objective is to evaluate the efficacy of an 8-week standardized Tuina therapy plus usual care (UC) compared to UC alone in reducing fatigue severity in patients with CFS. Secondary objectives include assessing effects on the clinical response rate, sleep quality, mental health, quality of life, and clinical global impression, as well as evaluating the safety of the intervention and the long-term sustainability of therapeutic effects up to 24 weeks after treatment.

### Trial Design

This study uses a prospective, multicenter, randomized, open-label, assessor-blinded, parallel-group design. The trial will be conducted at 6 clinical centers across China, with Shuguang Hospital affiliated to Shanghai University of Traditional Chinese Medicine serving as the leading center. The protocol has been developed in accordance with the SPIRIT (Standard Protocol Items: Recommendations for Interventional Trials) 2025 statement (Checklist 1) [17]. Table 1 outlines the major time points of this trial.

**Table 1. T1:** Schedule of enrollment, interventions, and assessments^a^.

Study period	Run-in	Allocation	Treatment	End of treatment	Follow-up	Follow-up	Other
Timepoint	Week −1 to 0	Week 0	Week 4	Week 8	Week 20	Week 32	Early withdrawal
Enrolment							
Informed consent	✓						
Eligibility screening	✓	✓					
Demographics	✓						
Medical history	✓						
Randomization		✓					
Interventions							
Tuina plus UC^b^			✓	✓			✓
UC			✓	✓			✓
Assessments							
CFQ-11^c^		✓	✓	✓	✓	✓	✓
SF-36 PF^d^	✓	✓	✓	✓	✓	✓	✓
SF-36 BP^e^		✓	✓	✓	✓	✓	✓
HADS^f^	✓	✓	✓	✓	✓	✓	✓
PSQI^g^		✓	✓	✓	✓	✓	✓
EQ-5D-3L		✓	✓	✓	✓	✓	✓
CGI^h^				✓			✓
Safety and other data							
Vital signs		✓	✓	✓			✓
Physical examination		✓	✓	✓			✓
Adverse events		✓	✓	✓	✓	✓	✓
Concomitant medications and therapies		✓	✓	✓	✓	✓	✓
UC log and consultation record		✓	✓	✓	✓	✓	✓
Adherence check			✓	✓			✓

a The “✓” symbol indicates that the item is scheduled at that time point.

b UC: usual care.

c CFQ-11: Chalder Fatigue Questionnaire.

d SF-36 PF: Short-Form 36 Physical Function Subscale.

e SF-36 BP: SF-36 Bodily Pain Subscale.

f HADS: Hospital Anxiety and Depression Scale.

g PSQI: Pittsburgh Sleep Quality Index.

h CGI: clinical global impression.

The study timeline is divided into three phases:

Run-in phase (day −7 to day 0): A 1-week screening period designed to confirm eligibility, ensure participant compliance, and collect stable baseline data (specifically depression levels and physical function) to serve as stratification factors for the subsequent randomization.Treatment phase (week 1 to week 8): Participants will receive the assigned intervention (Tuina plus UC or UC alone) for 8 consecutive weeks.Follow-up phase (week 9 to week 32): A 24-week posttreatment follow-up period to evaluate the long-term sustainability of the therapeutic effects.

### Patients and Recruitment

In this multicenter trial, patients with CFS will be recruited from outpatient clinics at 6 participating hospitals through advertisements on posters, WeChat, and hospital websites. Specialized physicians will confirm the diagnoses based on the 1994 Centers for Disease Control and Prevention (CDC) criteria, using comprehensive medical history taking, physical examinations, and necessary laboratory tests to exclude other organic or psychiatric causes of fatigue. To promote recruitment and retention, the treatment and relevant clinical assessments involved in the study will be offered free of charge to eligible candidates. Written informed consent will be obtained from all participants before the screening. Eligibility criteria are presented in a 2-column format in Textbox 1.

Textbox 1.Eligibility criteria.
**Inclusion criteria**
Diagnosis of chronic fatigue syndrome or myalgic encephalomyelitis according to the 1994 Centers for Disease Control and Prevention criteria [18], which includes the following:(1) persistent or recurrent fatigue lasting more than 6 months; (2) other organic diseases causing chronic fatigue must be excluded based on medical history, physical examination, or laboratory findings.The concurrent occurrence of at least 4 of the following 8 symptoms: (1) self-reported impairment in short-term memory or concentration; (2) sore throat; (3) tender cervical or axillary lymph nodes; (4) muscle pain; (5) multijoint pain without joint swelling or redness; (6) headaches of a new type, pattern, or severity; (7) unrefreshing sleep; and (8) post-exertional malaise lasting more than 24 hours.Age between 18 and 65 years (inclusive), with no gender restrictions.Willingness to participate in the study and capability to provide written informed consent.
**Exclusion criteria**
Secondary fatigue caused by other identifiable conditions, including infectious diseases, autoimmune disorders, malignancies, hypothyroidism, diabetes mellitus (and its complications), or drug-induced fatigue.Severe organic or unstable chronic diseases involving the cardiovascular, cerebrovascular, hepatic, renal, respiratory, or hematological systems.Long-term dependency on glucocorticoids with an inability to discontinue usage.High risk of bleeding, such as thrombocytopenia or coagulation disorders.Initiation of new treatments (pharmacological or non-pharmacological) for CFS or related symptoms within 14 days prior to enrollment.Skin conditions at the treatment sites or other physical conditions assessed by the investigator as unsuitable for Tuina therapy.Diagnosis of anorexia or anorexia nervosa.Severe psychiatric comorbidities, including schizophrenia, bipolar disorder, or current suicidal ideation.Severe obesity, defined as a BMI >45 kg/m².Pregnant or lactating women.Participation in another clinical trial within the past month or concurrent participation in other trials.Any other condition that, in the opinion of the investigator, renders the participant unsuitable for the study.

### Randomization and Blinding

Eligible participants will be randomized in a 1:1 ratio to either the intervention group (Tuina plus UC) or the control group (UC) via a central web-based randomization system (Interactive Web Response System [IWRS]). To ensure balance between groups across the 6 centers, the minimization method will be used. Stratification factors, based on baseline data collected at the end of the run-in phase, include:

Depression severity: Hospital Anxiety and Depression Scale (HADS)-Depression score (≤10 vs ≥11).Physical function: 36-item Short Form Health Survey (SF-36) Physical Functioning subscale score (≤40 vs ≥45).

### Allocation Concealment

The randomization sequence is generated by the IWRS and remains concealed from all investigators, therapists, and participants until the moment of assignment. Researchers will obtain the group assignment only after confirming eligibility and completing baseline assessments.

### Blinding

Because Tuina is a manual therapy, neither participants nor therapists can be blinded to group allocation. This open-label design may introduce performance and expectation bias. Moreover, most efficacy outcomes, including the 11-item Chalder Fatigue Questionnaire (CFQ-11), Pittsburgh Sleep Quality Index (PSQI), HADS, SF-36, and EQ-5D-3L, are patient-reported; therefore, assessor blinding provides limited protection against bias for these self-reported outcomes. This limitation is explicitly acknowledged and will be mitigated by standardized participant instructions, equal assessment schedules, electronic or paper questionnaire completion before clinical discussion, and separation of treatment providers from outcome assessors.

Outcome assessors responsible for collecting data will be blinded to group allocation and will not participate in treatment. The CGI will be assessed by clinicians who are blinded to allocation whenever feasible. Independent statisticians will analyze data using masked group codes until the primary analysis is finalized. Participants will be instructed not to disclose treatment details to assessors during follow-up visits.

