#### Secondary Outcomes

##### Clinical Response Rate

###### Overview

To evaluate the clinical significance of the treatment effect, the clinical response rate will be calculated at week 8. A responder is defined as a participant who achieves a reduction of ≥3 points in the CFQ-11 total score compared to baseline. This prespecified threshold was chosen as a conservative clinically meaningful improvement criterion informed by published work on minimal clinically important difference (MCID) for fatigue patient-reported outcome measures [23].

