### Global Impression

The Clinical Global Impression (CGI) scale will be used to assess the clinician’s global view of the patient’s illness and improvement [27]. It includes two subscales: Severity of Illness (CGI-S), rated on a 7-point scale from 1 (normal, not at all ill) to 7 (among the most extremely ill patients), and Global Improvement (CGI-I), rated from 1 (very much improved) to 7 (very much worse).

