### Strengths and Limitations

The study has several strengths. First, to our knowledge, this is the first large-scale, multicenter randomized controlled trial to investigate the efficacy and safety of Tuina therapy for CFS. The study design incorporates several methodological strengths to ensure rigor. Second, building upon our preliminary single-center pilot work, we have optimized the intervention protocol. We extended the treatment duration from 4 weeks to 8 weeks and the session length to 30 minutes. This dose optimization aligns with the chronic nature of CFS and aims to induce more stable, long-term therapeutic effects. A major challenge in manual therapy trials is operator variability [32]. Third, we have implemented a strict quality control system, including a unified SOP, centralized practitioner training, systematic treatment logs, and regular fidelity monitoring. This ensures that the intervention is reproducible across different clinical centers and allows cointerventions and concomitant medications to be described and explored in sensitivity analyses. Fourth, this trial includes a 24-week posttreatment follow-up, enabling evaluation of durability.

Several limitations should be acknowledged. First, because Tuina is a manual therapy, participant and therapist blinding is infeasible [33,34]. This open-label design may introduce performance or expectation bias. To mitigate this, we have implemented a strict assessor-blinded design, where outcome evaluators and statisticians are unaware of group allocations. Second, the primary outcome (CFQ-11) and key secondary outcomes are patient-reported measures, which are subjective. However, these scales are validated and widely accepted in CFS research, and we have included the CGI to provide a clinician’s perspective. Third, the study population is limited to patients meeting the CDC 1994 criteria; future research may need to explore efficacy across different diagnostic definitions (eg, Institute of Medicine or NICE criteria) to enhance generalizability.

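### The CGI, the only clinician-rated efficacy outcome, has no week 0 rating and only conditional rater blinding, which weakens but does not void it as a complement to the self-reports

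*Protocol article*

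**What the plan says.** **Schedule.** In Table 1 (Trial Design) the CGI row is ticked at week 8 and at early withdrawal only. CFQ-11, SF-36 PF, SF-36 BP, HADS, PSQI and EQ-5D-3L all have a week 0 tick.

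**Content.** Under Global Impression, the "scale will be used to assess the clinician’s global view of the patient’s illness and improvement". It has two parts: CGI-S, a 7-point rating of current severity, and CGI-I, a 7-point rating of improvement.

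**Rater blinding.** The Blinding section first says: "Outcome assessors responsible for collecting data will be blinded to group allocation and will not participate in treatment". The next sentence reads: "The CGI will be assessed by clinicians who are blinded to allocation whenever feasible". No fallback is given for the case where blinding is not feasible.

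**Role.** The same section concedes that most efficacy outcomes "are patient-reported; therefore, assessor blinding provides limited protection against bias for these self-reported outcomes". Strengths and Limitations says "we have implemented a strict assessor-blinded design, where outcome evaluators and statisticians are unaware of group allocations". After conceding that the patient-reported measures are subjective, it adds that "we have included the CGI to provide a clinician’s perspective".

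**Analysis.** Outcome Analysis assigns the CGI to proportional-odds models, or to nonparametric methods if the assumption fails, and names no baseline CGI term. As a week 8 secondary efficacy outcome, the CGI falls in the set adjusted by the Benjamini-Hochberg procedure.

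**The concern.** In an open-label trial whose other efficacy outcomes come from participants who know their allocation, the CGI is the one efficacy measure on which a blinded assessor can make a real difference. It is also the only efficacy outcome whose blinding is conditional, and the only efficacy scale not taken at week 0.

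Three things are at stake, all for a secondary outcome:

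- **Precision.** Without a baseline CGI-S there is no own-baseline covariate, no change score and no check of baseline balance on that scale.
- **Anchoring.** CGI-I asks the rater to judge improvement. With no recorded CGI-S, a rater who did not see the participant at baseline must reconstruct the starting point from other records or from the participant's account. The second route lets self-report back in.
- **Bias.** A rating made with knowledge of allocation can shift the between-group contrast. The plan neither limits the number of such ratings nor says that they will be identified.

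**Working it through.** **1. Is the CGI the only clinician-rated efficacy outcome?** The Blinding section lists CFQ-11, PSQI, HADS, SF-36 and EQ-5D-3L as patient-reported. The response rate is derived from one of them: "A responder is defined as a participant who achieves a reduction of ≥3 points in the CFQ-11 total score compared to baseline". Apart from safety, that leaves only the CGI.

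**2. Do the blinding statements agree?** Set side by side:

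| Place | Statement about raters |
|---|---|
| Blinding, on outcome assessors | blinded, no condition |
| Blinding, on CGI raters | blinded if feasible |
| Strengths and Limitations | evaluators unaware of allocation, design called strict |

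A CGI rater evaluates an outcome, so the second row is compatible with the other two only if blinding turns out to be feasible for every rating. The plan does not say that it will.

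**3. The plan's own figure.** No sample size is given for the CGI. The CFQ-11 calculation reproduces: the pooled SD is 6.208, which rounds to 6.21; a difference of 3.0 at 90% power and two-sided 5% gives 91.02 per group with the t distribution, rounded up to 92; and 92/(1 − 0.20) = 115. It is not in dispute. I use 92 per group below as the evaluable number.

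**4. What a baseline CGI-S would buy.** *Assumptions:* CGI-S treated as a standardised continuous score, linear adjustment, correlation ρ between baseline and week 8 of 0.3 to 0.7. The documents give no value for ρ.

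- Residual variance relative to no adjustment = 1 − ρ²
- Standard error = √[(2/92)(1 − ρ²)]
- Difference detectable at 90% power = standard error × (1.960 + 1.282)

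| ρ | 1 − ρ² | Variance reduction | Standard error | Detectable difference (SD) |
|---|---|---|---|---|
| 0 | 1.00 | – | 0.147 | 0.48 |
| 0.3 | 0.91 | 9% | 0.141 | 0.46 |
| 0.5 | 0.75 | 25% | 0.128 | 0.41 |
| 0.7 | 0.51 | 49% | 0.105 | 0.34 |

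This is a statement about precision only. Randomisation keeps the unadjusted week 8 comparison of CGI-S unbiased.

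**5. What unblinded ratings could do.** *Assumptions:* a share u of ratings is unblinded, and those ratings shift the between-group contrast by b SD. The bias is u × b. With s = u × b/√(2/92), the two-sided error rate at nominal 5% is 1 − Φ(1.96 − s) + Φ(−1.96 − s).

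| u | b | Bias (SD) | Error rate |
|---|---|---|---|
| 0 | any | 0 | 5.0% |
| 0.25 | 0.2 | 0.05 | 6.3% |
| 0.25 | 0.5 | 0.125 | 13.6% |
| 0.50 | 0.2 | 0.10 | 10.4% |
| 0.50 | 0.5 | 0.25 | 39.6% |

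Neither u nor b is in the documents. The table shows how the problem scales and that it vanishes when every rater is blinded.

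**The case against.** The case for leaving the plan alone is a fair one.

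- **Validity.** A week 8 CGI-S comparison is valid under randomisation without a baseline. CGI-I is itself a rating of change, so it has no baseline value to collect. Both points stand.
- **Records.** A reader might infer that the CGI-I rater must depend on the participant's recall. The documents do not show that. Table 1 provides a medical history at run-in and, at week 0, physical examination, vital signs and all the questionnaires; usual care, given in both groups, begins with a professional evaluation. Nothing says the rater is denied these. What remains is that none of them is a global severity rating on the scale being used.
- **Default.** A reader might also take the CGI to be an open-label rating. Blinded rating is the stated default, participants are told not to disclose treatment, and treatment providers are separated from outcome assessors. The objection to the conditional wording is that it is unbounded and unrecorded.
- **Claim.** The article offers the CGI only as a clinician's view, openly admits the limits of assessor blinding for self-reports, and calls the secondary outcomes supportive and exploratory. It is therefore too strong to say that the CGI cannot complement the self-reports, or that it will be presented as independent confirmation.
- **Size.** The variance figures rest on an assumed correlation and a linear formula, whereas the planned model is proportional odds on a 7-point scale. They also compare with no adjustment at all; other baseline measures could recover part of the gain. This stands, so the figures are illustrative.

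None of this explains why the CGI alone lacks a week 0 rating, or removes the conflict between the blinding statements.

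**Conclusion.** The point holds in a limited form: the CGI is a weakened, not a void, complement to the self-reports. Two facts rest on the text alone: it has no week 0 rating, and its rater blinding is stated in ways that conflict.

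The first costs precision and anchoring. Under the linear approximation with an assumed correlation of 0.3 to 0.7, the residual variance of week 8 CGI-S would be 9% to 49% lower with a baseline; no figure is offered for CGI-I. The second can bias the comparison, but only in proportion to the unblinded share. With a quarter to a half of ratings unblinded and a shift of 0.2 to 0.5 SD, all assumed, the nominal 5% error rate would be about 6% to 40%; with none unblinded it stays at 5%.

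The primary CFQ-11 analysis and the sample size are not touched. The change is worth making because it is cheap, and because a pre-treatment severity rating cannot be obtained for a participant once treatment has begun.

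**What to change.** 1. **Add CGI-S at week 0, before randomisation.** Group assignment is already released only after baseline assessments are complete, so this rating would be blind to allocation by construction. Make it available to the week 8 rater as the anchor for CGI-I.
2. **Use it in the analysis.** Include baseline CGI-S as a covariate in the week 8 proportional-odds models for CGI-S and CGI-I.
3. **Make rater blinding a rule.** Require that the CGI rater be a clinician who does not treat the participant and is blinded to allocation. The article does not say that the existing outcome assessors are clinicians, so each centre should confirm who can fill this role.
4. **Record the rater's blinding status at every rating** and report a sensitivity analysis by that status. State the caveat that excluding unblinded ratings conditions on an event after randomisation, possibly related to arm and response, and so may itself introduce selection.
5. **Reconcile the text.** If full blinding of CGI raters cannot be guaranteed, soften Strengths and Limitations to match the Blinding section.

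The cost is one short extra rating at an existing visit, one field on the case report form, minor analysis work, and possibly a clinician's time at centres where the assessors are not clinicians.
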